## 3.0 SELECTION AND ENROLLMENT OF PARTICIPANTS

### 3.1 Number of Participants

The trial will enroll 988 participants across all five hospital sites in Toronto, Canada.

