### 8.4 Questionnaires and/or Scales

Questionnaires will be electronically administered weekly through REDCap, which will be emailed to participants directly (consent will be granted for email contact). Those lacking email/internet access may complete questionnaires on paper and/or by interview by study staff (may be done remotely). Then, weekly, all participants will be asked to complete self-report of COVID-19 symptoms/testing/outcomes/time off work, and adherence. For participants with confirmed COVID-19, questions will also include symptom duration, hospitalization, respiratory support and time ineligible/unable to work due to COVID-19. An email reminder will be sent for each questionnaire at day three of each weekly cycle and repeated twice.

The same online system will be used to measure study drug adherence, using a modified version of the ACTG adherence scale. This scale was developed by the AIDS Clinical Trials Group to assess adherence to antiretroviral therapy. This scale is brief, easy to use, and was rigorously developed, with high internal consistency and construct validity among adults taking antiretroviral therapy for HIV. Results will be scored according to the included items from this scale.

Finally, at day 1, 60 and 120, participants will also be asked to complete the K10, a short ten-item scale to measure non-specific psychological distress. A standard cutoff score of  $\geq 16$  will be used to define short-term psychological distress.

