### 11.2 Sample Size Considerations/Justification

The 3-month risk of infection in healthcare workers not treated with prophylaxis was assumed to be 10%. This corresponds to a hazard of 0.035 infections per month under the assumption of exponentially-distributed time to infection. Reducing 3-month risk to ~6% was judged to be both feasible and clinically important; this reduction corresponds to a hazard ratio of 0.588. With a one-sided type I error rate of 5%, to have 80% power, to detect this hazard ratio, a total of 92 events are needed. Using the event rates above and exactly 3 months + 14 days planned follow-up for each participant, a total of 988 participants need to be randomized. These calculations account for the single interim analysis described below.

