### 11.3 Endpoints/Outcome Measures

#### 11.3.1 Analysis of Primary Outcome Measures

The primary outcome comprises a microbiologically confirmed COVID-19 infection and the date of the confirmatory test. At the date of an analysis (interim or final), each participant will have either an infection and date of infection, or a known uninfected status and time since randomization (censoring date). The rates of the outcome will be

compared between randomized groups using a Cox proportional hazards model with stratification by site (used in the stratified randomization) and inclusion of job class as a covariate. As there are too many distinct job classes in the inclusion criteria for them all to be included in the model, they will be grouped before any analysis begins. The grouping will combine classes of job deemed to be at similar levels of exposure, while keeping groups a reasonable size. If there is heterogeneity in risk by job class, inclusion of this factor in the analyses increases power with compromising type I error. See section 9.5 for details on inference at the interim and final analyses. A plot of cumulative incidence of infection over the 104-day study period will be made for each group and the overall rates of infection in each study arm will be calculated. All primary analyses will be by intention-to-treat. While loss to follow-up is expected to be low, if more than 5% of participants withdraw, missing data will be imputed under a variety of assumptions, to assess the robustness of our findings.

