### 11.3.2 Analysis of Secondary Outcome Measures

**Adverse events** will be tabulated by study arm. The percentages of participants experiencing each type of AE, or any AE will be calculated by severity level. The rate per 100 person-days will also be calculated by AE and severity level. If warranted, AEs will be compared between groups using the methods for the primary analysis. **Symptom duration, duration of hospitalization due to COVID-19 disease, days of respiratory failure requiring ventilatory support attributable, and number of days ineligible/unable to work due to COVID-19** will be summarized within group by the median and interquartile range as well as the mean. As the majority of participants will have zero for all of these outcomes, a bootstrap hypothesis test, with stratification by site, will be used to test the hypothesis of no treatment effect. A 95% confidence interval for the mean difference in days will also be computed using the bootstrap. Mortality is expected to be very low, so will simply be summarized by a count and percentage in each arm. The relative risk of mortality by 90 days will be calculated if feasible. **Seropositivity** will be analyzed by the same approach described for the primary outcome. **Short-term psychological impact of exposure to COVID-19** as measured by the K10 will be summarized by group at each of the three time points (day 1, 60, and 120), using the mean and standard deviation as well as the percentages with scores at or above the standard cutoff score of 16. As the trial is blinded, there is no expectation of a direct effect of treatment on the K10. Those who become infected may have higher scores, so results will also be presented according to the previous occurrence of an infection. The primary comparison of this outcome will use a linear model to estimate the effect on 60-day values of site, study arm, and job class, using the day 1 value as a covariate. The relative risks of exceeding the threshold at 60 days for these same variables will be estimated in a log-binomial model with the same covariate. The change in K10 between days 60 and 120

will be estimated to assess whether there is a reduction in psychological impact once participants know they are on prophylaxis with an active drug.

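### With at least moderate correlation between Day 1 and Day 60 K10, the planned log-binomial model lands on the edge of its allowed range, so its fits and model-based intervals are unreliable (minor point)

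*Protocol*

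**What the plan says.** Section 8.4 describes the K10 as "a short ten-item scale to measure non-specific psychological distress", completed at Days 1, 60 and 120. Section 11.3.2 makes the primary comparison a "linear model to estimate the effect on 60-day values of site, study arm, and job class, using the day 1 value as a covariate". It then adds a second, binary analysis, in which "relative risks of exceeding the threshold at 60 days for these same variables will be estimated in a log-binomial model with the same covariate". Hence the covariate carried over is the Day 1 score as a number, and the relative risks wanted are those for arm, site and job class.

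The descriptive summary in the same section uses the "percentages with scores at or above the standard cutoff score of 16". Sections 2.4 and 8.4 set the same cut-off, 16 or more. Section 11.3.2 says nothing on handling the upper bound on risk, on a fallback estimator, or on how intervals for these relative risks are to be formed. No K10 mean, SD or Day 1-Day 60 correlation is given anywhere.

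**The concern.** A log-binomial model makes log risk a straight line in each numeric covariate. A distress score measured twice in the same people is likely to be correlated, so most people with high Day 1 scores will again score 16 or more at Day 60, and their risk levels off near 1. A log line cannot level off. It keeps rising until it meets the limit of 1 at the highest Day 1 scores in the data, and a handful of such people then fix the slope for everyone.

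At stake are the relative risks for arm, site and job class. They could come from an invalid fit, or carry intervals that are too narrow. The job-class ratios have some interest of their own: the synopsis and Section 2.1 treat occupation as a proxy for exposure risk, and Section 2.3 aims to describe distress linked to that risk. If the fit breaks down, the analyst must choose a substitute after seeing the data.

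**Working it through.** **Plan figures.** The protocol has no planning figure for the K10 model. Its events figure for the primary outcome ("With a one-sided type I error rate of 5%, to have 80% power, to detect this hazard ratio, a total of 92 events are needed") reproduces by Freedman's formula: (1.645 + 0.842)² × (1.588/0.412)² = 6.18 × 14.86 = 91.9, so 92. Nothing below touches it.

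**Inputs from the protocol.** Model, covariate and cut-off are as quoted from Section 11.3.2. On size, Section 3.1 states "The trial will enroll 988 participants across all five hospital sites". On job classes, Section 11.3.1 says "they will be grouped before any analysis begins" and gives no number of groups.

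**Assumed inputs.** Score range 10-50; 940 analysed (988 × 0.95 = 939); 4 site groups and 4 job groups; mean K10 14-22, SD 4-7; correlation r between Day 1 and Day 60 of 0.3-0.7; no true effect of arm. These give 25-84% at or above 16 on Day 60. Scores were drawn as shifted gamma variables joined by a Gaussian copula.

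**Step 1, the constraint.** With ηᵢ = xᵢ'β and risk pᵢ = exp(ηᵢ), the fit maximises Σ[yᵢηᵢ + (1 − yᵢ)log(1 − exp ηᵢ)] subject to every ηᵢ ≤ 0. This is a concave problem, so the constrained maximum can be found exactly. A fit was counted as on the boundary if any fitted risk came within 0.0001 of 1.

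**Step 2, why the model-based SE shrinks.** The information is Σ[pᵢ/(1 − pᵢ)]xᵢxᵢ'. At risks of 0.25 and 0.84 the weight is 0.33 and 5.25. At 0.99 it is 99, and at 0.9999 it is 9,999. About 2-6 people near the boundary can therefore supply most of the apparent information.

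**Step 3, boundary and coverage.** Each row is 500 simulated trials. Coverage is for the nominal 95% interval of the arm relative risk. The log-binomial SE is model-based, with fitted risks essentially uncapped.

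| Mean, SD | r | On boundary | Log-binomial coverage | Modified Poisson coverage |
|---|---|---|---|---|
| 14, 4 | 0.5 | 96.6% | 84.6% | 94.2% |
| 16, 5 | 0.5 | 99.2% | 77.4% | 93.0% |
| 18, 6 | 0.3 | 93.4% | 92.2% | 95.6% |
| 18, 6 | 0.5 | 99.8% | 77.2% | 95.8% |
| 18, 6 | 0.7 | 100% | 63.6% | 93.8% |

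Over all settings run, the boundary was reached in 95.5-100% of trials at r = 0.5, in 100% at r = 0.7, and in 56-100% at r = 0.3 (lowest at mean 14). Log-binomial coverage was 71-87%, 59-66% and 85-94% respectively. Job-class intervals behaved like the arm interval: about 81% at r = 0.5 and 58-62% at r = 0.7. Capping fitted risks at 0.99 when computing the SE raises arm coverage to 84-91% at r = 0.5-0.7, which is still short of 95%.

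**Step 4, cross-check on the SE.** At mean 18, SD 6, r = 0.7, the model-based SE of the arm log relative risk was 0.0326, and its actual SD over simulations was 0.0658. The half-width 1.96 × 0.0326 = 0.0639 is 0.97 actual SDs, which implies about 67% coverage, in line with the table. For modified Poisson at r = 0.5 (same mean and SD) the SE was 0.0526 against an SD of 0.0514. Then 1.96 × 0.0526/0.0514 = 2.01, or about 95.5%.

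**Step 5, standard software.** Ordinary iterative fitting in seven settings gave a valid interior solution in 0-12% of trials. In 54-90% it reported convergence with a fitted risk of 1 or more, and in 9-34% it failed or raised an error.

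**Step 6, where the problem fades.** The boundary was reached in 7% of trials at r = 0.1, in 22-41% with a logistic slope of 0.1 per point and Day 1 scores capped at 30, and in 1-40% when risk was truly log-linear and stayed below 1.

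**The case against.** - **Dependence on unstated inputs.** A reader might infer that the model fails for almost any K10 data. The documents do not support that: they give no K10 distribution or correlation, and Step 6 shows settings where the boundary is reached in a minority of trials. This objection stands, and the point is limited to moderate or stronger correlation.
- **False-positive rate.** Someone looking only at strongly correlated settings might quote 20-40% false positives throughout. At r = 0.3 coverage is 85-94%, so that figure does not apply generally.
- **Non-convergence.** It is tempting to say that software simply will not converge. More often it reports convergence with an impossible fitted risk, which is easier to overlook.
- **No interval method is fixed.** Section 11.3.2 only says that these ratios are estimated, and it uses a bootstrap elsewhere. The undercoverage assumes model-based intervals, and a statistical analysis plan not seen here may name a fallback. It may also code Day 1 K10 as below or at least 16, which gave 0% boundary fits and 94% coverage. This softens the point but does not remove it, because the protocol itself names the estimator and the numeric covariate is its plain meaning.
- **Threshold wording.** *Exceeding* might be read as a different cut-off from *at or above*. Taken literally it would reclassify a score of exactly 16, but Sections 2.4, 8.4 and 11.3.2 all define 16 or more. This is loose wording, not a conflict over the threshold.
- **Small stake.** The K10 is the last-listed secondary outcome, the binary model supports a linear one, and no direct drug effect is expected. This stands in full.

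**Conclusion.** The point holds as a minor one. If Day 1 K10 enters as a number and correlates with Day 60 K10 at about 0.5 or more, the planned model reaches its boundary in nearly every trial, standard fits are mostly invalid, and model-based 95% intervals cover about 71-87% (r = 0.5) or 59-66% (r = 0.7). At r = 0.3 the loss is mild. The figures rest on assumed K10 distributions, and the coverage figures also rest on the use of model-based standard errors.

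A reader might infer that the trial's conclusions on K10 or on efficacy are at risk. They are not: the linear model on Day 60 scores is the primary K10 comparison, and the time-to-infection analysis does not use this model.

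**What to change.** In Section 11.3.2, or in the statistical analysis plan, replace the log-binomial model by modified Poisson regression (log link, robust variance) with the same terms: arm, site, job class and Day 1 K10. This keeps the conditional relative risk already planned. Its coverage was 93-96% in the 500-trial runs and 91-98% in shorter ones. Logistic regression standardised over the sample to a relative risk is an alternative; if it is chosen, state that the target becomes a marginal relative risk.

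Word the event as K10 of 16 or more at Day 60, to match Sections 2.4 and 8.4. The cost is one sentence, settled before analysis, with no new data and no change to sample size.

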### 11.3.3 Interim Analysis

One interim analysis of the primary outcome is planned when half the expected number of events (46/92) has occurred. The table below shows the properties of this design. At the first interim analysis, a Z-statistic ( $-\log(\text{HR})/(\text{Standard Error})$ ) larger than 2.67 will be taken as evidence of efficacy; this is the same as checking whether the one-sided p-value is  $< 0.0038$ . If the true hazard ratio is 0.588 (as in the sample size calculation), there is a 19% chance of stopping for efficacy at this interim analysis. The trial may stop for futility (with the recommendation coming from the DSMC, as this is a non-binding futility boundary) if the Z-statistic is less than -0.01, which corresponds to the one-sided p-value being  $> 0.51$ . If the true HR is 1.0, there is a 49% chance that the interim analysis will cross this futility boundary. If the trial does not stop for futility or efficacy, the final analysis will take place at the earlier of the date that all participants have reached the end of the 104-day randomized or when 92 events have occurred. This final analysis will declare superiority of HCQ over placebo if the Z-statistic is  $> 1.65$  (or the one-sided p-value is  $< 0.049$ ). With 92 total events, power is 80% against  $\text{HR}=0.588$  and type I error is 5% across the whole trial. One-sided testing is justified here to increase power, as there is no interest in concluding that HCQ is inferior to placebo. A finding other than HCQ being superior will lead to the same decision not to use it.

| Analysis   | Value                        | Efficacy | Futility |
|------------|------------------------------|----------|----------|
| IA 1: 50%  | Z                            | 2.6700   | -0.0142  |
| N: 988     | p (1-sided)                  | 0.0038   | 0.5057   |
| Events: 46 | HR at bound                  | 0.4542   | 1.0042   |
| Month: 1.7 | P(Cross) if $\text{HR}=1$    | 0.0038   | 0.4943   |
|            | P(Cross) if $\text{HR}=0.59$ | 0.1864   | 0.0365   |
| Final      | Z                            | 1.6549   | 1.6549   |
| N: 988     | p (1-sided)                  | 0.0490   | 0.0490   |
| Events: 92 | HR at bound                  | 0.7076   | 0.7076   |
| Month: 3.5 | P(Cross) if $\text{HR}=1$    | 0.0489   | 0.9511   |
|            | P(Cross) if $\text{HR}=0.59$ | 0.8000   | 0.2000   |

At the final analysis, the hazard ratio, its 90.2% confidence interval will be calculated, as the upper limit of the 90.2% CI will lie below 1 if the null hypothesis that HR=1 is rejected.

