## 7.3 Drug Safety and Monitoring Board

Risk minimization, management, and assessment procedures have been implemented in the study to minimize and assess potential risks to participants who participate in this clinical study with HCQ. Components include: (1) specific study entry and exclusion criteria to ensure that participants who have underlying condition that potentially increase their risk for an adverse outcome are excluded; (2) overview surveillance by an independent Data Safety Monitoring Board (DSMB); (3) follow-up (monthly) for safety monitoring purposes at in-person study visits.

The DSMB will include infectious diseases and public health specialists, at least one biostatistician, and researchers with an understanding of emerging infections and clinical trials, not involved in the trial. The DSMB will meet after half the expected number of infections have occurred in the trial. The purpose of the DSMB will be to review safety concerns, conduct and review the interim analysis and review external data that may have bearing on the design of or decision to continue the trial. The committee will meet at

further 1 month intervals and provide feedback to the principal investigator; however, the responsibility for the final decision regarding a DSMB-recommended course of action will rest with the principal investigators.

In the event that the outbreak has ended at one or more study sites and the study has not yet been completed, the study should be paused. Efficacy data from the trial must not be prematurely released. In this instance, the DSMB should conduct an interim analysis of the study data to make recommendations whether the study should continue or stop for efficacy, futility or safety. As per World Health Organization policies on data-sharing in a Public Health Emergency, clinical trial outcome data will be shared at the earliest possible opportunity.

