#### 8.2.2 Microbiologic testing for SARS-CoV-2

Specimens for viral RNA testing will be collected at each study visit. Participants will be instructed on self-collection of nasopharyngeal, oropharyngeal, nasal and/or oral swabs or saliva for RT-PCR testing and specimens will undergo biobanking if not tested in real-time for future analysis. The final collection method to be used in the study will be made based on the availability of the collection kits for the study. If oropharyngeal/nasal swabs are not available, saliva will be collected. Self-collection of swabs has been validated in multiple other settings and will allow for reduced exposure to study staff. These tests are for the purposes of investigating asymptomatic COVID-19 infection (as per the protocol any symptomatic participants will be tested through the most appropriate institutional methods – ie. occupational health or the ED). Specimens will be extracted using an automated system (easyMAG) and real-time PCR conducted using primers and probes against genes encoding the RNA-dependent RNA polymerase (RdRp) and the envelope (E) protein of COVID-19. Quantitation against a standard curve will be calculated in RNA copies/microliter.

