#### 8.2.3 SARS-CoV-2 Serology

Methods for serologic testing of COVID-19 are still in development worldwide at the time of writing, but are rapidly emerging. Participants will undergo venipuncture at baseline, and monthly until and including the 120 day visit and samples processed into plasma for frozen storage by [name] laboratory (co-PI). Frozen samples will be batch-tested in the laboratory of Co-I [name] at the conclusion of the study when methods are finalized.

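### The interim is set on a composite whose serology is untested until the study ends, and the DSMB's first meeting waits for half the expected infections with no date of its own

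*Protocol*

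**What the plan says.** All references are to the protocol.

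- **Endpoint.** Section 2.4 counts a participant as infected on any positive validated assay, either viral RNA or seroconversion, by day 104.
- **Interim.** Section 11.3.3: "One interim analysis of the primary outcome is planned when half the expected number of events (46/92) has occurred". Section 11.3.1 says that at any analysis, interim or final, each participant has a dated infection "or a known uninfected status and time since randomization (censoring date".
- **Serology.** Section 8.2.3 freezes the monthly plasma and batch-tests it "at the conclusion of the study when methods are finalized".
- **Scheduled viral samples.** Section 8.2.2: "specimens will undergo biobanking if not tested in real-time for future analysis". Under Section 9.6, home samples stay in the participant's freezer until the next monthly visit.
- **Symptomatic infections.** Under Section 2.4 these are tested through routine hospital channels and the study collects the results.
- **Final analysis.** Section 11.3.3 sets it at 92 events or when everyone has finished the 104-day period, whichever comes first.
- **DSMB.** Section 7.3: "The DSMB will meet after half the expected number of infections have occurred in the trial". Monthly meetings follow that one. The board is also to run an interim analysis if the outbreak ends at one or more sites with the study unfinished.

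**The concern.** The protocol fixes the interim endpoint, its trigger and the assay timing, and the three do not fit together. Seroconversion status does not exist when the interim is due, and RNA status from scheduled swabs may not exist either. No section limits the interim count to RNA-confirmed infections or orders an early serology batch.

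Two things are at stake. First, a stop for efficacy or futility could rest on a different outcome from the one the trial was sized for and will finally report. The infections sure to be visible are those found by symptom-prompted testing, so an effect of the drug on symptoms alone could look like an effect on infection at the interim and shrink once serology is read. Second, Section 7.3 names independent DSMB surveillance as a risk-minimisation measure, but its only scheduled start is an infection count.

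**Working it through.** **Inputs.** Control 3-month risk 10%, hazard ratio 0.588, one-sided 5%, 80% power, 92 events, N = 988 (Section 11.2); 1:1 allocation (Section 5.1); bounds Z = 2.67, -0.0142 and 1.6549 (Section 11.3.3); enrolment 20 April 2020 to 30 July 2021 (Synopsis), which is 466 days or 15.31 months. The share *s* of infections found only by end-of-study testing is not given, so it is an assumption shown as a range.

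**1. The plan's own figures reproduce.**
- Control hazard: -ln(0.90)/3 = 0.03512 per month.
- Events, Schoenfeld: 4(1.645 + 0.842)²/(ln 0.588)² gives 88. Freedman: (1.588/0.412)² × (1.645 + 0.842)² gives 92, as stated.
- Interim efficacy stop at HR 0.588: 1 - Φ(2.67 - 0.531 × √46/2) = 0.19. Futility stop at HR 1: Φ(-0.0142) = 0.49. Both agree with Section 11.3.3.
- Time to 46 events if all 988 start together: 494 × [2 - exp(-0.03512t) - exp(-0.588 × 0.03512t)] = 46 gives t = 1.71 months, the table's 1.7.

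The fault is therefore not in the design arithmetic.

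**2. Can 46 events be seen while the trial runs?** Over 3 months + 14 days (3.46 months) the planned rates give 90.6 composite events. Countable events are 90.6 × (1 - s). The probability of at least 46 uses a normal approximation to the two binomial counts. When 46 have been counted, about 46/(1 - s) infections have occurred.

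| s (assumed) | Countable | P(at least 46) | Infections when 46 counted |
|---|---|---|---|
| 0 | 90.6 | 1.00 | 46 |
| 0.2 | 72.5 | 1.00 | 57.5 |
| 0.3 | 63.4 | 0.99 | 65.7 |
| 0.4 | 54.4 | 0.89 | 76.7 |
| 0.5 | 45.3 | 0.49 | 92 |
| 0.6 | 36.2 | 0.06 | not expected |

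A low attack rate does the same with every event visible. Control risk 6% gives 54.3 events (P = 0.89), 5% gives 45.3 (P = 0.49) and 4% gives 36.2 (P = 0.06).

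The probability of counting 92 in real time is 0.46 at s = 0 and 0.01 at s = 0.2. The 104-day rule would then set the final analysis.

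**3. Type I error.** With the printed efficacy bounds and futility ignored (it is non-binding), type I error is 1 - Φ₂(2.67, 1.6549; ρ = √r) at information fraction r. It is 0.051 at r = 0.3, 0.050 at r = 0.5 and 0.049 at r = 0.83. It cannot exceed 0.0038 + 0.0490 = 0.0528.

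**4. When would the DSMB first meet?** Assume uniform entry over 15.31 months (988/15.31 = 64.5 per month), 104 days (3.417 months) of follow-up each, planned rates and every infection visible. At month 9.547:
- Past day 104: (9.547 - 3.417) × 64.53 = 396 participants. Mean 104-day risk is (0.1131 + 0.0681)/2 = 0.0906, giving 35.8 events.
- Still in follow-up: 3.417 × 64.53 = 220 participants. Mean risk so far is the average over arms of 1 - (1 - e^(-hF))/(hF), with F the 104-day follow-up: (0.0577 + 0.0345)/2 = 0.0461, giving 10.2 events.
- Sum: 46.0 events, with 396 + 220 = 616 randomised.

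At s = 0.3 the same calculation gives month 12.9, with about 613 past day 104.

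**The case against.** Much can be said for the plan.

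- **The trigger is not invisible.** Symptomatic infections are tested and recorded, the weekly questionnaire collects results, and Section 8.2.2 permits real-time swab testing. Counting 46 RNA-confirmed infections proves the trigger has passed. This stands.
- **The final analysis has a fallback** in the 104-day rule. This stands, although the text does not say that it waits for stored-sample results.
- **Safety is watched in other ways:** monthly visits, repeat QTc measurement, 24-hour SAE reporting, a Medical Monitor and the outbreak-ends route to the DSMB. This stands as mitigation, but the first four are not review by an independent board and the last is contingent.
- **Serology methods were still in development**, so an early batch may not have been possible. That is a reason to define the interim on RNA-confirmed infections, not to leave it undefined.
- **Section 2.1 describes the primary outcome as symptomatic, microbiologically confirmed COVID-19**, which routine testing would largely reveal. But the Synopsis outcome measures and Section 2.4 define the composite, and Section 2.1 itself allows time for seroconversion.

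Stronger readings are tempting and fail. A reader might infer that 46 visible events at s = 0.3 represent 71% information (65.7/92). They do not: information in a Cox Z comes from the events entering the statistic, so 46 counted of 92 is still 50%. A reader might infer that the stated 19% and 49% stopping probabilities no longer apply. Under the null, Z is about standard normal whichever events are counted, so 49% holds; 19% holds if the hazard ratio for RNA-confirmed infection is also 0.588. A reader might call month 1.7 an error. It is a projection under simultaneous entry, and no decision rule uses it.

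**Conclusion.** The concern holds in two parts.

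1. Sections 2.4, 11.3.1 and 11.3.3 require an interim on the composite with known status for everyone, and Sections 8.2.2 and 8.2.3 make that impossible. The interim would in practice be an RNA-confirmed analysis that censors undetected infections as uninfected. The harm is a mismatch of endpoint between interim and final, and a trigger detected late. It is not inflated type I error, which stays at 4.9% to 5.1% for information fractions from 0.3 to 0.83. How far the hazard ratio for RNA-confirmed infection might differ from the composite one cannot be derived from the protocol.

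2. The only scheduled first DSMB meeting depends on infections. At planned rates, with uniform entry (assumption) and full visibility, it falls at about month 9.5, with about 616 randomised and about 396 already past day 104.

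A reader might conclude that the triggers can never be observed or that the DSMB will never meet. The documents do not support that as a general statement. Failure to reach 46 needs about half or more of infections to be serology-only, or a control risk near 5% or below instead of 10%. Neither figure is in the protocol.

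**What to change.** 1. Reconcile Sections 2.4, 8.2.2, 8.2.3, 11.3.1 and 11.3.3, and say which events count toward 46 and 92. Either batch-test the stored blood and viral samples collected up to the interim cut, so that interim and final use the same composite; or, if no assay is ready, define the interim explicitly on RNA-confirmed infections, with bounds from the spending function at the actual number of counted events. Name that function. The printed efficacy bound matches a Hwang-Shih-DeCani spend with parameter -5: 0.05 × (1 - e^2.5)/(1 - e^5) = 0.0038, Z = 2.67.
2. State in Section 11.3.3 that the final analysis waits for the stored-sample results.
3. In Section 7.3, set the first DSMB safety review by calendar or enrolment, independent of infections (for example, when the first 100 participants reach Day 30), and keep the monthly interval.

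The cost is one extra assay batch if the first option is chosen, an earlier meeting of an existing board, and protocol wording.
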